### Sample size and power

Based on the primary outcome of the completion of ACP documentation and assuming a completion rate of around 37% for the control group, with a total of 86 participants/dyads (43 per group) we will be able to show a significant improvement to 67% completion for the VDST group (power of 80%, two sided 5% significance level). Assuming an estimated dropout rate of 30%, recruitment of 112 dyads will be required. Based on previous published studies, we felt that a sample of this size would give us sufficient methodological experience to conduct a subsequent fully powered study [12].

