#### Data collected and measures used

Table 3 outlines the measures used at baseline and post-intervention. The baseline questionnaire will include the patient’s and caregiver’s demographic information, including age, sex, marital status, place of birth, the relationship between patient and caregiver, primary cancer diagnosis, and length of time living with the diagnosis. Patients will be asked if they had previously discussed prognosis with their doctor.

**Table 3 Tab3:** Measures used pre and post UC and VDST

Measures used	Patient		Caregiver	
	Baseline: Pre UC/VDST	Post UC/VDST	Baseline: Pre UC/VDST	Post-UC/VDST
Demographics	**×**		**×**	
DASS-21	**×**			
ACP Attitudes	**×**	**×**	**×**	**×**
CCAT	**×**	**×**	**×**	**×**
PDMS	**×**	**×**	**×**	**×**

*DASS-21* Depression, Anxiety and Stress Scale, *CCAT* Cancer Communication and Assessment Tool, *PDMS* Preparation for Decision Making Scale

The following variables and outcomes will be assessed:

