*Baseline Depression, Anxiety and Stress scores*. The DASS 21 scale is a validated 21 item self-reported questionnaire designed to measure the negative emotional states of depression, anxiety, and stress [35]. Evaluation of the DASS 21 in cancer has shown acceptable internal consistency reliability for the Depression subscale (α = .90) and Anxiety subscale (α = .70) with construct validity to measures of suicidal ideation, quality of life, self-rated health, and depressed mood [36].*Attitudes towards ACP*. Understanding of, opportunities, distress, and confidence related to ACP will be assessed using a previously designed and tested questionnaire comprising nine patient and eight caregiver items, measured on a 10 point Likert scale [32].*Congruence in decision-making* will be measured using the Cancer Communication Assessment Tool for Patients and Families (CCAT-PF). CCAT-PF consists of 18 items and measures congruence in patient-caregiver communication with the analogous patient (CCAT-P) and family (CCAT-F) instruments, exploring preferences, values, and experiences in treatment decision-making. The CCAT-PF demonstrated internal reliability coefficients for the CCAT-P (α = .52), CCAT-F (α = .50), and CCAT-PF (α = .60). Higher CCAT-PF scores are significantly correlated with greater patient depression and perceived family conflict, lower patient-caregiver assessment and well-being, and less expressiveness and family cohesion [37].*Preparation for decision-making* will be measured using the Preparation for decision-making scale, a validated scale assessing patient and caregiver perception of an intervention’s usefulness. Psychometric analysis has shown Alpha coefficients for internal consistency ranging from 0.92 to 0.96 and that the scale discriminated significantly between patients who did and did not find a decision aid helpful (*p* < 0.0001) [38].

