## Statistical analysis

Descriptive statistics will be presented as frequencies and relative frequencies for categorical variables, mean and standard deviation for normally distributed continuous variables, or median and interquartile range for continuous variables that are not normally distributed. We will examine secondary outcomes between the two groups comparing pre and pre and post-test intervention changes with Chi-square or Fisher’s exact test for categorical variables and two-sample *t*-tests or Mann-Whitney test for continuous variables.

Additionally, multiple linear regression will be performed, addressing the effect of socio-demographic and clinical variables to explore factors associated with the rates of completion of ACP All results obtained will be presented at a confidence interval of 95%. Thus *p* < 0.05 is assumed to be statistically significant. The statistical software SPSS 23 will be used in this analysis.

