### Limitations

There remains a paucity of literature on the methodological challenges that may arise with video vignettes’ development. Even the most realistic scripted video vignettes may differ from communication as it naturally unfolds. It is suggested that the manipulation of less defined concepts such as ‘the communication of values’ in our study through video vignettes poses specific challenges due to challenges in operationalizing such concepts.

Intervention studies in cancer cohorts typically demonstrate significant attrition rates due to progressive illness and high mortality [41]. Cancer patients also not uncommonly remain ambivalent or choose to relinquish or reject ACP as they potentially elicit death anxiety or other existential distress forms. Finally, this study provides an intervention at a single time point, is restricted to a single site and will not measure subsequent congruence between documented ACP decisions and EOL outcomes. It also limits recruitment to English-speaking participants with no provision made for those with limited health literacy and cannot participate.

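### The only stated model for ACP completion is an exploratory linear regression that does not name arm; one prespecified logistic model with arm and two baseline covariates would use information the trial already collects

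*Protocol article*

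**What the plan says.** In the protocol article, Statistical analysis states that "multiple linear regression will be performed, addressing the effect of socio-demographic and clinical variables to explore factors associated with the rates of completion" of ACP. The between-group tests in that section (chi-square or Fisher, t-test or Mann-Whitney) are unadjusted and attached to the secondary outcomes. No test is named for the primary outcome.

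Sample size and power treats completion as yes/no, "assuming a completion rate of around 37% for the control group" and 67% for the video group, with 43 dyads per group, 80% power and a two-sided 5% level. It adds: "Assuming an estimated dropout rate of 30%, recruitment of 112 dyads will be required".

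Data collected and measures used lists ACP attitudes at baseline for patient and caregiver: "Understanding of, opportunities, distress, and confidence related to ACP will be assessed using a previously designed and tested questionnaire". It also says: "Patients will be asked if they had previously discussed prognosis with their doctor". Randomization and blinding places randomisation after the baseline assessments, in blocks of 6, and mentions no stratification factor. Limitations remarks: "Cancer patients also not uncommonly remain ambivalent or choose to relinquish or reject ACP as they potentially elicit death anxiety".

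**The concern.** The one sentence that brings covariates to the primary outcome uses them to look for correlates of completion. It does not use them to sharpen the comparison of the arms. It also fixes a linear model for an outcome that the sample size section handles as a proportion.

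The trial holds at least one variable that plausibly relates to completion. The protocol gives ambivalence and death anxiety as reasons for refusing ACP, and the baseline attitude questionnaire covers distress and confidence about ACP. Because it is completed before randomisation, arm cannot affect it.

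With about 40 dyads per group and no stratification described, the groups can differ by chance in readiness for ACP. A model with arm and a readiness score would remove part of that noise. What is at stake is precision and some power. The validity of the trial is not in question.

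**Working it through.** **1. The plan's own figure.** Inputs from Sample size and power: p1 = 0.37, p2 = 0.67, difference 0.30, mean 0.52, two-sided 5%, power 80%.

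n = [1.960 × √(2 × 0.52 × 0.48) + 0.842 × √(0.37 × 0.63 + 0.67 × 0.33)]² / 0.30²
= [1.960 × 0.7065 + 0.842 × 0.6739]² / 0.09 = 42.3, so 43 per group.

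This matches the protocol. Power at 43 is 80.6%. The figure is therefore that of a crude two-proportion comparison.

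**2. Number left after dropout.** 112 × 0.70 = 78.4, about 39 per group, where the same formula gives 76.6%. (The target of 112 is 86 × 1.3; 86 / 0.7 gives 123.) Both 43 and 39 are carried forward.

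**3. Effect of adjustment by formula.** If covariates explain a share R² of outcome variance within arm, both standard errors shrink by √(1 − R²):

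power = Φ[(0.30 − 1.960 × SE0 × √(1 − R²)) / (SE1 × √(1 − R²))], with SE0 = 0.7065/√n and SE1 = 0.6739/√n.

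The protocol gives no R², so a range is shown. Gains are taken before rounding.

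| Assumed R² | Power, 43 per group | Gain (points) | Power, 39 per group | Gain (points) |
|---|---|---|---|---|
| 0 | 80.6% | 0 | 76.6% | 0 |
| 0.02 | 81.4% | 0.8 | 77.4% | 0.9 |
| 0.05 | 82.6% | 2.0 | 78.7% | 2.2 |
| 0.10 | 84.7% | 4.0 | 80.9% | 4.4 |
| 0.15 | 86.7% | 6.1 | 83.2% | 6.6 |
| 0.20 | 88.7% | 8.0 | 85.4% | 8.8 |

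**4. Simulation, two covariates.** Marginal rates were held at 37% and 67%, with two normal covariates of equal strength. There were 10,000 trials per row; the logistic likelihood-ratio column uses the first 6,000.

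| R² | n per group | Chi-square | Linear model with arm | Logistic model with arm |
|---|---|---|---|---|
| 0 | 43 | 80.3% | 79.9% | 81.0% |
| 0.05 | 43 | 79.8% | 82.0% | 83.0% |
| 0.09 | 43 | 79.4% | 83.2% | 84.0% |
| 0.14 | 43 | 79.7% | 85.5% | 87.0% |
| 0 | 39 | 77.4% | 75.4% | 76.6% |
| 0.05 | 39 | 77.4% | 77.7% | 78.8% |
| 0.09 | 39 | 78.4% | 80.2% | 81.2% |
| 0.14 | 39 | 77.1% | 81.5% | 82.4% |

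At 43 the linear model gains about 2 to 6 points, in line with the formula. At 39 the gain is smaller than the formula suggests. In a null run at 43 per group, type I error was 5.6% (chi-square), 5.1% (linear) and 5.7% (logistic likelihood ratio), so part of the logistic column's advantage reflects a slightly liberal test. A separate run with the Wald test and one covariate gave 4.7% to 5.1%.

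**5. One useful and one useless covariate.** Logistic Wald test against Pearson chi-square, 8,000 trials per row, with an uninformative binary second covariate. At 39 per group, the change by log-odds slope of the first covariate was:
- slope 0: −1.6 points
- slope 0.2: −1.2
- slope 0.3: −0.7
- slope 0.4: none
- slope 0.6: +0.9
- slope 0.9: +3.6

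At 43 per group, slope 0 lost 0.4 points and slope 0.6 gained 3.1.

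**The case against.** The strongest objection is that this argues from silence. A condensed article may leave the primary model to a full protocol or analysis plan, and sizing a trial on a crude contrast does not bar an adjusted analysis. A reader might infer that the plan excludes arm from the model, or rules out any use of the baseline variables. The text does not support that. No primary test is stated, no full covariate list is given, and the prognosis question could count as a clinical variable. What stands is narrower: the one completion model that is described is framed as factor-finding, does not name arm, and is linear.

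A second objection is that the link between the covariates and completion is assumed. Limitations gives reasons for refusing ACP, but it does not say that the attitude score captures them or predicts completion. This stands, and it is why the gain is shown as a range.

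A third is that adjustment has a price. This also stands: in step 5 the two-covariate model loses power at 39 per group when one covariate is useless and the other weak.

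Finally, in a randomised pilot the crude comparison is valid, and its type I error already allows for chance imbalance. That is correct. Nor would a linear model be fatal if it contained arm: in the null run it held its level. Logistic regression is preferred because it suits a yes/no outcome and keeps fitted probabilities between 0 and 1.

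**Conclusion.** The point holds as an efficiency improvement that is worth making. As described, the baseline ACP-attitude score and prior prognosis discussion do not reach the treatment effect on completion.

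The size is conditional. At 43 per group, the gain is about 2 to 6 points if the covariates explain 5% to 15% of outcome variance, about 1 point at 2%, and about 0 if they explain nothing. At 39 per group, simulated gains are smaller, and uninformative covariates cost about 1 to 2 points.

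Three stronger conclusions are tempting, and the documents do not support them: that the trial is known to give up 2 to 6 points, that adjustment is free, and that an unadjusted comparison would be wrong.

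**What to change.** Replace the regression sentence with one prespecified model for the arm effect: logistic regression of ACP completion (yes/no) on arm, baseline patient ACP-attitude score (mean per item) and prior prognosis discussion (yes/no). Report the adjusted odds ratio and the standardised risk difference, each with 95% CI, beside the crude proportions by arm. The standardised difference is the average over all patients of the predicted probability under the video tool minus that under usual care. Fix the covariates before any outcome data are seen. If the search for factors associated with completion is kept, label it exploratory and separate from this model.

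The cost is a few lines of wording and no new data. A simple rule for missing baseline items is needed, for example the mean of the items answered. The Abstract calls the questionnaire anonymous, so baseline answers must be linked to completion by a study code; the planned pre-post changes need such a link anyway. The statistical cost is the possible loss of about 1 to 2 points of power at 39 per group if the covariates prove uninformative.

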## Discussion

We present the protocol for a pilot randomised control trial developed as part of a body of work exploring ACP in cancer in the Australian setting. This study follows from previous studies conducted by members of the research team, demonstrating the feasibility and acceptability of the written vignette technique, recruitment of patient-caregiver dyads, and completion of ACP’s. The use of video vignettes as a decision aid is supported by a Cochrane review of 115 RCTs involving 34,444 participants showing that compared to UC, decision aids improve knowledge, accurate risk perception, likelihood of selecting options congruent with personal values, and reduce decisional conflict [39]. The video vignette technique has been proven to be acceptable and effective in several North American settings and, it is possible that this equally effective in the Australian setting [12].

A novel aspect of this study is the use of video vignettes to promote values discussion. The use of video to explore a values-based ACP paradigm has been shown to be successful in a single study [40]. This approach’s potential benefit in increasing the uptake of ACP in cancer care may allow for more meaningful EOL care planning between patients and their families. Our use of patient-caregiver dyads is relatively unique to ACP video intervention studies. This is despite evidence that suggests the benefit of congruence in communication between patient and caregiver, particularly in the cancer setting [22].

### Limitations

There remains a paucity of literature on the methodological challenges that may arise with video vignettes’ development. Even the most realistic scripted video vignettes may differ from communication as it naturally unfolds. It is suggested that the manipulation of less defined concepts such as ‘the communication of values’ in our study through video vignettes poses specific challenges due to challenges in operationalizing such concepts.

Intervention studies in cancer cohorts typically demonstrate significant attrition rates due to progressive illness and high mortality [41]. Cancer patients also not uncommonly remain ambivalent or choose to relinquish or reject ACP as they potentially elicit death anxiety or other existential distress forms. Finally, this study provides an intervention at a single time point, is restricted to a single site and will not measure subsequent congruence between documented ACP decisions and EOL outcomes. It also limits recruitment to English-speaking participants with no provision made for those with limited health literacy and cannot participate.

## Conclusion

We need to continue to explore innovative ways to engage cancer patients in ACP. This pilot study’s findings will assist with further refinement of the VDST and planning for a future multisite study.

## Data Availability

Not applicable. Data sharing is not applicable as this article has no datasets that have been generated or analysed yet. The datasets generated during the study will be available from the corresponding author on reasonable request.

## Abbreviations

ACP: Advance care planning;
CCAT: Cancer Communication Assessment Tool
CCAT-P: Cancer Communication Assessment Tool for Patient
CCAT-F: Cancer Communication Assessment Tool for Families
CCAT-PF: Cancer Communication Assessment Tool for Patient and Families
EOL: End-of-life
MEPOA: Medical Enduring Power of Attorney
MTDM: Medical Treatment Decision Maker
UC: Usual care
VDST: Video decision support tool
